## Abstract

**Introduction:** In the primary care (PC) setting in Spain, the prevalence of emotional disorders (EDs) such as anxiety, depression and somatoform disorder is high. In PC patients, these disorders are not always managed in accordance with the recommendations provided by clinical practice guidelines, resulting in major direct and indirect economic costs and suboptimal treatment outcomes. The aim is to analyze and compare the cost-effectiveness and cost-utility of group-based psychological therapy versus treatment as usual (TAU).

**Methods:** Multicenter, randomized controlled trial involving 300 patients recruited from PC centers in Madrid, Spain, with symptoms or possible diagnosis of anxiety, mood (mild or moderate), or somatoform disorders. Patients will be randomized to one of two groups: an experimental group, which will receive group-based transdiagnostic cognitive-behavioral therapy (TD-CBT); and a control group, which will receive TAU (mainly pharmacological interventions) prescribed by their general practitioner (GP). Clinical assessment will be performed with the Patient Health Questionnaire (PHQ). Direct and indirect costs will be calculated and relevant socio-demographic variables will be registered. The Spanish version of the EuroQol 5D-5L will be administered. Patients will be assessed at baseline, immediately after treatment finalization, and at 6 and 12 months post-treatment.

**Discussion:** To our knowledge, this is the first study to compare TD-CBT to TAU in the PC setting in Spain. This is the first comparative economic evaluation of these two treatment approaches in PC. The strength of the study is that it is a multicenter, randomized, controlled trial of psychotherapy and TAU for EDs in PC.

**Trial registration:** Protocol code: ISCRCTN58437086; 20/05/2013.

EUDRACT: 2013-001955-11.

Protocol Version: 6, 11/01/2014.

## Introduction

Emotional disorders (EDs)—especially anxiety, mood, and somatoform disorders—are the most prevalent types of mental disorders in Spain (Haro et al., 2006). As in many countries, individuals in Spain suffering from EDs typically first consult with their PC GP for diagnosis and treatment. According to a recent study in Spain (Serrano-Blanco et al., 2010), the 12-month prevalence rate for mental disorders among users of the Spanish PC system was 31.2% in Catalonia (Spain). Eighteen point 5% of the patients fulfilled criteria for an anxiety disorder and 13.4% for depression, which are associated with chronic pain, gastrointestinal disorders, and other chronic physical conditions.

Medical treatment usually involves the prescription of psychoactive drugs, most commonly anxiolytics. However, according to clinical practice guidelines, medical therapy is not the treatment of choice; rather, for most EDs, the initial treatment recommendation is psychological therapy. Given this tendency in the Spanish system to prescribe medications, it is not surprising that anxiolytic use in Spain is much higher than in other countries. According to a recent report (OECD, 2015), the median DDD of anxiolytics per 1000 inhabitants in Spain was 52.3 doses—double the median rate (22.3 DDD) reported by the OECD.

The high use of psychoactive drugs in Spain reflects not only the prevalence of EDs, but also underscores the burden of these illnesses. According to Lara et al. (2015), neuropsychiatric disorders were the leading cause of disability for all illnesses in the year 2010, and depressive and anxiety disorders—together with the use of psychopharmacological substances—were the conditions that most contributed to the increase in years lived with disabilities. In view of the above, to accurately assess the costs originated by these disorders, it is essential to consider not only the direct costs of health system utilization, but also the indirect economic burden caused by lost or reduced productivity (Ruiz-Rodríguez et al., 2017).

The total economic cost for mental disorders in Spain is high, but precise figures are not known because published estimates vary widely. According to 2002 administrative data, these costs were estimated to be approximately 1% of the GDP (Oliva-Moreno et al., 2009). By contrast, a more recent estimate of the costs of brain disorders (mental and neurological disorders) in Spain (Parés-Badell et al., 2014), based on rigorous clinical studies on the prevalence and costs of each disease, found that the costs were nearly €84 billion in the year 2010 (approximately 8% of GDP). Remarkably, these costs exceeded the total medical public expenditure, which was €69 billion (6.6% of GDP). According to that study, the costs of mental disorders (excluding neurological disorders) amounted to €46 billion (4.4% of GDP), with depressive, anxiety and somatic disorders accounting for nearly half (€22 billion; 2.2% of GDP) of the total for all mental disorders.

Despite the high prevalence of both anxiety and depressive disorders in Spain, one study found that only 30.5% of PC patients and 31.8% of specialized care patients received “minimally adequate” evidence-based treatment (Fernández et al., 2006). The reason(s) for this lack of adherence to evidence-based clinical practice guidelines is unclear. Consequently, more research is needed to investigate this question so that steps can be taken to improve physician adherence to guidelines and, thereby, improve treatment effectiveness and reduce treatment-related costs, particularly those associated with prescription medications.

Poor adherence to clinical guidelines is not unique to Spain. In the year 2007, a similar problem was identified in the United Kingdom, ultimately leading to the development of a program entitled “IAPT” designed to promote the treatment of EDs in PC with CBT in accordance with the NICE recommendations (NICE, 2011). That initiative has been very successful, resulting in substantially improved treatment outcomes while simultaneously reducing costs (particularly due to decreased drug prescriptions) compared to the usual PC treatment (Radhakrishnan et al., 2013). Indeed, given the success of the IAPT program with EDs, the program has been extended for use in children and in patients with chronic physical conditions (Gyani et al., 2013). Due to the considerable savings of the CBT approach versus drug-based therapies, one recent study estimated that even if the number of patients treated with CBT in the PC setting doubled (from 500,000 to 1 million per year), the net cost would likely be zero if patients with common mental disorders (anxiety and depression) and those with comorbid chronic physical conditions receive CBT (Layard and Clark, 2015).

In Spain, a randomized controlled clinical trial [the Psychology in Primary Care (PsicAP) study] is currently in progress to compare evidence-based psychological techniques [such as transdiagnostic (TD)-CBT] to treatment-as-usual (TAU) (Cano-Vindel et al., 2016) in patients with EDs. Given this context, the present work describes the design of a study being conducted as part of the PsicAP clinical trial (sub-study 2). The aim of this sub-study is to assess and compare the costs associated with psychological and pharmacological treatment approaches for mental disorders in the PC setting in Spain. This study will assess the relationship between cost-effectiveness and cost-utility of these two different treatment approaches. We hypothesize that the costs of switching from TAU to a group-based TD-CBT approach will be justified by the expected additional clinical and social benefits (a superiority trial).

## Methods and Analysis

### Study Design

This a multicenter (see **Appendix 1**, list of PC Centers), randomized controlled trial carried out in Madrid, Spain. Patients will be randomly allocated to one of two groups—an experimental group and a control group—both of which will be treated in a PC setting. The experimental group will receive group-based CBT and the control group will receive TAU (mainly pharmacological interventions). Evaluators will be blinded to the treatment group allocation throughout the evaluation period.

### Patient Recruitment

Patients from the participating PC centers will be recruited by their GP who will provide patients with a document containing detailed information about the study. All patients will be required to sign an informed consent form prior to enrolment. The GP will provide the researchers with the patients’ contact information and relevant data so that the psychologists can arrange a screening test to determine patient eligibility.

The study inclusion criteria for the first phase of recruitment, which will be managed by the GP, are as follows: (1) age range, 18–65 years; (2) previous history of anxiety, depression, or somatoform disorders; (3) WHO ICD-10 criteria for anxiety, depression or somatoform disorders; (4) diagnostic evaluation or clinical suspicion of the presence of at least one of these disorders.

In the second phase of recruitment, clinical psychologists will consider the following inclusion criteria: (1) age, 18–65 years; (2) presence of emotional symptomatology (anxiety, depression, or somatization) with suspected diagnosis of anxiety (generalized or panic attacks), mood (mild and moderate), or somatoform disorders. All candidates will be assessed with the PHQ (Spitzer et al., 1999). The Spanish version validated by Diez-Quevedo et al. (2001) will be used, except for the GAD module, which will be replaced by the GAD-7 validated Spanish version developed by García-Campayo et al. (2012). Patients will be considered eligible for study inclusion if they meet the criteria (based on a decision tree algorithm) for a likely diagnosis of one of these disorders or if the patient has a score ≥ the cut-off score for any of the following PHQ subscales: GAD-7 (generalized anxiety ≥ 10); PHQ-9 (depression ≥ 10); PHQ-13 (somatizations ≥ 5); PHQ-PD (panic attack, ≥ 8 for the first four items of that scale).

Exclusion criteria include the following: diagnosis of a severe mental disorder, such as bipolar or personality disorder (both those described in the patient’s clinical history, treated by specialized mental health services, and those detected through the clinical diagnostic interview, in the second phase of recruitment); presence of a recent, severe suicide attempt; high impairment scores (≥25) on the Sheehan Disability Scale (Sheehan et al., 1996); and legal disability. Additional exclusion criteria include: presence of severe anxiety disorder (e.g., comorbid with substance-use disorders) and/or severe mood disorder (PHQ-9 ≥ 20). Participants who score between 20 and 23 points on the PHQ will undergo a second order assessment conducted by a clinical psychologist to confirm the existence of severe major depression, and any patients with major depression will also be excluded from the trial. Patients will not receive any financial compensation for their participation in the study.

### Sample Size

Two programs were used to determine sample size: (a) G^∗^Power3 (Faul et al., 2007) which prioritizes statistical power, and (b) SSS-CET (Software for Sample Sizes in Cost Effectiveness Trials) which uses a Bayesian approach (Sarker et al., 2013). Based on these analyses, a sample size of 176 participants per group was established (*N* = 352). However, it should be noted that previous investigations have proven that 150 participants are sufficient for a cost-effectiveness study (Rubio-Valera et al., 2013, 2015). Thus, the sample size established for this study is 150 participants per study group (*n* = 300).

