### Main Outcomes

The main outcomes are the clinical symptoms assessed by the PHQ: depression, anxiety, panic, and somatic symptoms, as well as economical variables and EuroQol 5D outcomes in terms of QALYs.

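### The plan reports a calculated requirement of 176 per group but adopts 150 per group on precedent alone, 14.8% below its own figure and without restating what 150 can detect

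*Protocol article*

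**What the plan says.** The Sample Size section opens with the calculation: "Two programs were used to determine sample size", one aimed at statistical power (G*Power) and one a Bayesian tool for cost-effectiveness trials (SSS-CET). The result is stated without qualification: "Based on these analyses, a sample size of 176 participants per group was established", or 352 in total.

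The section then departs from that result. It says that "previous investigations have proven that 150 participants are sufficient for a cost-effectiveness study" and concludes: "Thus, the sample size established for this study is 150 participants per study group". The Abstract carries the smaller number, describing a "randomized controlled trial involving 300 patients recruited from PC centers in Madrid, Spain".

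Other sections bear on how the number should be read:

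- The Introduction calls this a superiority trial.
- Main Outcomes lists several endpoints together: "The main outcomes are the clinical symptoms assessed by the PHQ: depression, anxiety, panic, and somatic symptoms, as well as economical variables", and also QALYs from the EuroQol questionnaire. The Sample Size section does not say which of these either number serves.
- Retention foresees patients who drop out of treatment, and Analysis of Clinical Effectiveness provides for imputation when more than 5% of values are missing. Neither is linked to the sample size.

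**The concern.** A protocol may enrol fewer patients than its calculation asks for, provided it says what is given up. This one states a requirement, sets a smaller number, and presents the smaller number as sufficient.

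The reason offered does not carry that weight. Power and precision depend on the effect, variability, outcome and losses in the trial at hand, so a size used elsewhere cannot by itself show that 150 is enough here. The precedent is also ambiguous: the 150 could be a total or a group size, and the plan applies it per group. It is invoked for cost-effectiveness only, whereas the main outcomes include four symptom domains.

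What is at stake is how the results are read. The section names a power program and a calculated size, so a reader may assume that 300 has the power or precision intended for 352. It does not, and the plan does not say by how much it falls short.

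**Working it through.** **Inputs from the protocol article.** Calculated size 176 per group (352 in total) and adopted size 150 per group (300 in total), both from Sample Size. Equal allocation is implied by the equal group sizes. Alpha, sidedness, power, effect size, standard deviation and dropout rate are not stated.

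**Step 1. Can 176 be reproduced?** Not from stated inputs. One familiar combination matches it: a two-sample t-test, two-sided 5%, 80% power and a standardised difference d = 0.30 needs 175.4, rounded up to 176 per group. Another fits equally well: 90% power with d = 0.346. A match of this kind does not show which calculation was done, and one of the two programs is Bayesian.

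**Step 2. What follows without assuming inputs.**

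- Shortfall per group: 176 − 150 = 26; in total 352 − 300 = 52.
- Relative shortfall: 26/176 = 14.8%.
- For a comparison of two means at fixed alpha and power, the detectable difference is proportional to 1/√n. The ratio is √(176/150) = 1.083, about 8% larger. The same factor applies to the width of a confidence interval whose standard error scales with 1/√n.

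**Step 3. Power at 150, under labelled assumptions.** Assume a two-sample comparison of means at two-sided 5%, with 176 evaluable per group giving the target power. The effect size then cancels. In the normal approximation,

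power(n) = Φ[(1.960 + z_target) × √(n/176) − 1.960].

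For an 80% target, 1.960 + 0.842 = 2.802. At n = 150, 2.802 × √(150/176) = 2.586, less 1.960 gives 0.626, and Φ(0.626) = 0.734. The t-based calculation gives the same to three decimals. The t-based results for four targets are below; 120 per group is 150 less an assumed 20% loss.

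| Power assumed at 176 | Implied d | Power at 150 | Power at 120 |
|---|---|---|---|
| 80% | 0.299 | 73% | 64% |
| 85% | 0.320 | 79% | 70% |
| 90% | 0.346 | 85% | 76% |
| 95% | 0.385 | 91% | 84% |

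The loss is about 4 to 7 percentage points before dropout and 11 to 16 points after an assumed 20% loss. One-sided calculations at 150 differ by about 1 point at most.

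**Step 4. What if 176 already included a dropout allowance?** The text does not say. 176 × 0.85 = 149.6, so 176 is also compatible with about 150 evaluable patients plus a 15% loss. But 150 is the planned number of participants, so the same 15% loss would leave 150 × 0.85 = 127.5. The ratio 127.5/149.6 = 0.852 equals 150/176. The factor of 1.083 and the power at 150 in the table are therefore unchanged, but they would then describe the trial after that loss, and the last column would not apply.

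**The case against.** The strongest defence has four parts.

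- **The reduction is disclosed.** Both numbers are printed, so nobody is misled about the size. This stands, and it lowers the severity. It does not supply a reason for the smaller number.
- **An article condenses the full protocol.** Alpha, power, effect size and dropout rate may be given there. This also stands: their absence is not the point here. The point is what the article does state, a calculated requirement followed by a smaller number declared sufficient by precedent.
- **The sub-study is mainly about estimation.** Its stated aim is cost-effectiveness and cost-utility, reported as incremental ratios, with bootstrap intervals for the cost-utility ratios, so fewer patients mainly mean wider intervals. This is partly right, and is why the restatement should cover precision as well as power. But the plan also claims superiority and lists symptom scores among its main outcomes.
- **Any power figure is a guess.** This is right for any single figure. It does not touch the 14.8% shortfall or the factor of 1.083.

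A reader might go further and infer that the trial has 73% power for d = 0.30, or that the 352 contains no dropout allowance. The documents support neither: no inputs are given, and the text is silent on an allowance. Nor can one say how the earlier studies differ from this trial in intervention, variance or effect, because they are not shown.

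**Conclusion.** The point holds in this form. The protocol article states a requirement of 176 per group and plans 150, and no other section justifies the difference. The shortfall of 26 per group (14.8%) follows directly from the two printed numbers. The increase of about 8% in the detectable difference at equal power needs only the usual 1/√n scaling. Expected dropout comes off the 150.

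The power figures rest on assumptions: a two-sample comparison of means, two-sided 5%, 176 evaluable per group giving between 80% and 95% power, and a 20% loss for the lower set. On these, power is about 73% to 91% at 150 per group and about 64% to 84% at 120. They show the scale of the gap and should not be quoted as the trial's power.

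This should be fixed, but it does not invalidate the design. Handling of the several main outcomes is a separate matter and would not close the gap between 176 and 150.

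**What to change.** In the Sample Size section:

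1. Keep 300 if that is the intended size, and say plainly that it is below the calculated 352.
2. Delete the claim that 150 is proven sufficient. Give the sponsor's actual reason for the smaller number; the documents do not state one, so a label such as feasibility should be used only if the sponsor confirms it.
3. From the actual inputs behind the 176, restate the power or detectable difference at 150 per group, and the expected precision of the cost-effectiveness estimate, before and after expected dropout.
4. Name the outcome to which the restated figure refers, and say whether the 176 already included a dropout allowance.

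The figures printed should be the sponsor's, not the back-calculated ones above. The cost is one paragraph and a stated power less favourable than the original calculation implied. No extra patients are needed. If the sponsor wants to keep the original target instead, the alternative is to return to 176 per group, with any dropout allowance made explicit.

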#### Assignment of Interventions

##### Allocation

After informed consent is obtained, participants are randomly assigned to either the treatment or control group by a researcher, according to a blind research design, using a computer-generated allocation sequence, thus assuring comparable groups on main outcomes. Each group will include approximately 8–10 patients randomly allocated to the experimental (TD-CBT) or control group (TAU). Subjects will receive the allocation information via email from a graduate student trainee affiliated with the project. The email will also provide login details and website information for the allocated intervention.

##### Blinding

One clinical psychologist will be assigned to the TD-CBT group; importantly, the clinical psychologist involved in the pre- and post-treatment assessment phases will not participate in the TD-CBT therapy. Data managers and statisticians will also be blinded to the treatment allocation.

The flowchart of the study is summarized in **Figure 1**.

**FIGURE 1 F1:**
[figure not shown]
Flowchart of the study.

### Interventions

#### Experimental Group

The treatment program is included within a collaborative protocol of a stepped-care model of treatment, as recommended by the NICE (2011) guidelines. The first step involves group TD-CBT based on a treatment manual [Cordero-Andrés et al., 2017; González-Blanch et al., 2017; Cano-Vindel (Unpublished)]. The characteristics of this treatment have been described previously by Cano-Vindel (2011). EDs are believed to originate from a dual process of dysfunctional emotional learning over time that involves both cognitive (increasing use of cognitive distortions) and associative (classical conditioning in some significant emotional events) learning. Although this dysfunctional learning tends to lead to symptom chronicity and the development of new, comorbid disorders, the process is considered to be reversible. Moreover, both types of functional relearning (i.e., cognitive and associative) can be achieved with cognitive-behavioral techniques such as cognitive restructuring and behavioral exposure. A transdiagnostic approach (Newby et al., 2015), which involves simplification and economy of resources by applying similar therapeutic procedures to different EDs, will be used in this group intervention. However, the unique characteristics of the cases in each group will be taken into consideration.

Patients in the experimental group will be divided into subgroups of approximately eight patients each and will be treated by clinical psychologists specifically trained for this program. The intervention will include seven sessions (1.5 h/session) delivered over a 24-week period. The contents include the following: psychoeducation, cognitive restructuring, relaxation, behavioral training, and relapse prevention.

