#### Description of Cost Analysis

Direct costs of health care will be estimated by adding the costs derived from medication use (antidepressants, hypnotics, sedatives, and anxiolytics), medical tests, use of health-related services, and staffing costs. The cost of medications will be calculated by determining the price per milligram (mg) during the study period according to the Vademecum International (Vidal, 2014), including value-added tax. Total costs of medications will be calculated by multiplying the price per mg by the daily dose (mg) and the number of days of drug treatment.

The main source of unit cost data related to public medical tests and use of health services will be obtained from the fee information published by the Official Government Journal of the Autonomous Community of Madrid (2013). Indirect costs will be calculated according to the number of days on sick leave multiplied by the minimum daily wage in Spain for 2015 (€21.62). Finally, total costs will be calculated by summing the total direct and indirect costs. The unit costs will be expressed in Euros (€) based on 2015 prices.

Currently, there is no reference fee for the TD-CBT intervention that will be used with the experimental group. The estimated cost of a consultation with a public sector GP in Spain is €39 (not including complementary tests). Given that salaries for psychologists in Spain are similar to those of GPs, we will use this amount (€39) to calculate the cost of the TD-CBT intervention (i.e., €39 multiplied by the number of assessment and treatment sessions, €39 × 9 = €351). Since the GP consultation fees are understood to include the cost of office space, we will not add any additional costs for office rent to the cost of the therapy. Accordingly, the total cost of the evaluation and psychological intervention (nine sessions) per person is estimated at €43.87 (€351/8).

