### Protocol Amendments

Six protocol amendments have been presented during the course of this trial:

*Amendment 1:* One PC center was added to the autonomous communities of the Basque Country and was approved by the Clinical Research Ethics Committee of Euskadi (CEIC-E). Also, a sub-study (sub-study 1) was presented to conduct the study of the psychometric properties of the PHQ subscales of the PHQ-9, PHQ-PD, and GAD-7 with 15% of the larger sample. This sub-study has been conducted in four PC centers located in the autonomous communities of Valencia (1 center), Balearic Islands (1), Basque Country (1) and Castilla la Mancha (1). The sub-study was also approved by the three first local Ethics Committees: the CEIC-APCV, the Clinical Research Ethics Committee of the Hospital Universitario de Albacete (CEIC-HUA), the Clinical Research Ethics Committee of Euskadi (CEIC-E), and the Clinical Ethics Committee of the Balearic Islands (CEI-IB).

*Amendment 2:* Nine centers located in the Community of Madrid were added to the study. The Clinical Research Ethics Committee of Madrid approved this amendment, as did the national Ethics Committee, the CEIC-APCV.

*Amendment 3:* One PC center was added to the group of centers in the autonomous community of Valencia. This center thus becomes a full participant in the trial and the sub-study (bring the number of PC centers in sub-study 1–5). Also, several changes to the first version of the protocol were made, including the use of the SCID-I to confirm severe MMD and questions to confirm high disability on the SDD, as described above. Also, new researchers were added to the study. The amendment was approved by the national Ethic Committees (the CEIC-APCV) and by the relevant local ethics committees.

*Amendment 4:* Three PC centers, two in Andalusia (2) and one in Cantabria (1), were added to the list of participating centers. Also, sub-study 2—a study of the cost-efficiency measures that are conducted in the PC centers in Madrid and Valencia—was presented. Several changes to the next version of the protocol were made, including the telephone follow up post-treatment (see “*Therapist Training”* section above). Finally, new researchers were added to the study. The amendment was approved by local Ethic Committees, the Clinical Research Ethics Committee of Córdoba (CEI-C), and the Clinical Ethics Committee of the Cantabria (CEIC) and national Ethic Committee, the CEIC-APCV.

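### TD-CBT is priced at a fixed €351/8 for every patient, although the protocol lets group size vary and costs other resources on recorded use (minor; direction not fixed)

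*Protocol article*

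**What the plan says.** Group size appears twice. The Experimental Group section states: "Patients in the experimental group will be divided into subgroups of approximately eight patients each". The Allocation section states: "Each group will include approximately 8–10 patients randomly allocated to the experimental (TD-CBT) or control group (TAU").

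The price is set in Description of Cost Analysis. No reference fee exists for TD-CBT, so the GP consultation fee stands in: "we will use this amount (€39) to calculate the cost of the TD-CBT intervention". Nine assessment and treatment sessions at €39 make €351, and "the total cost of the evaluation and psychological intervention (nine sessions) per person is estimated at €43.87 (€351/8"). The divisor is the planned size of eight. Nothing there links it to the groups formed, the number allocated to each, or the sessions held.

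Other resources are handled differently. The Economic Assessment section records visits, tests, hospital use, and each drug's dose and duration. Description of Cost Analysis multiplies the price per mg by daily dose and days of treatment, and days of sick leave by €21.62.

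The mean cost difference is the numerator of both the cost-effectiveness and the cost-utility ratio. The Cost-Utility Analysis section draws 1000 bootstrap samples for the interval of the latter. The Sensitivity Analysis section promises a robustness check without naming the parameters to be varied.

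**The concern.** A group session costs the same whether six or ten patients are in the group, so the cost per patient depends on the group actually formed. The plan lets that size vary but prices it as if it did not.

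Two things follow. First, the cost of the treatment that defines the experimental arm has no link to delivery, whereas the mainly pharmacological control treatment is costed on what was used. Any gap between planned and realised size shifts the mean cost difference systematically, and more resampling cannot remove that shift. Second, a constant has zero variance, so the bootstrap interval leaves out all variation between groups in intervention cost.

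**Working it through.** **Inputs from the protocol article**
- Session price €39, nine sessions, divisor 8 (Description of Cost Analysis).
- Seven treatment sessions (Experimental Group), which leaves 9 − 7 = 2 assessment sessions.
- TD-CBT arm: "the sample size established for this study is 150 participants per study group" (Sample Size).
- Madrid centres (Protocol Amendments): "Nine centers located in the Community of Madrid were added to the study" under Amendment 2, and two more under Amendment 5.

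**Assumptions**
- 9 or 11 centres take part. Appendix 1, which lists them, is not shown.
- Groups are formed within a centre, with at most 10 patients each.
- Patients per centre are not given, so an even or a random spread is used.

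**Step 1. Reproduce the stated price.** 39 × 9 = 351, and 351/8 = 43.875, printed as €43.87. It reproduces.

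**Step 2. Price by actual group size m, as 351/m.**

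| m | € per patient | against €43.87 |
|---|---|---|
| 6 | 58.50 | +33% |
| 7 | 50.14 | +14% |
| 8 | 43.88 | 0% |
| 9 | 39.00 | −11% |
| 10 | 35.10 | −20% |

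Within the Allocation section's range of 8–10, a divisor of 8 gives the highest price. Below 8 the stated price is too low.

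**Step 3. Can the groups be filled?** A centre with n patients splits wholly into groups of 8–10 if 8g ≤ n ≤ 10g for some whole number g.
- 9 centres, even spread: 150/9 = 16.7, so six centres have 17 and three have 16. Each splits into two groups of 8 or 9.
- 11 centres, even spread: 150/11 = 13.6, so seven centres have 14 and four have 13. That is more than 10 and fewer than 16, so no such split exists. Two groups of 6 or 7 result.
- 11 centres, uneven spread: six centres with 9, one with 16 and four with 20 make 54 + 16 + 80 = 150, and every group fills.

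**Step 4. Arm mean, as 351 × (number of groups)/150.**
- 9 centres, even: 18 groups, mean size 8.3, 351 × 18/150 = €42.12 (−€1.75).
- 11 centres, even: 22 groups, mean size 6.8, 351 × 22/150 = €51.48 (+€7.61, or +17%).
- Random spread with equal probability per centre, 20,000 draws: 9 centres, mean €44.5 (95% range 42.1 to 49.1); 11 centres, mean €47.4 (42.1 to 51.5).
- A strict maximum of 8 would raise the upper end: 9 centres, even, need 24 groups, 351 × 24/150 = €56.16 (+€12.29). The article's wording sets no such maximum.

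**Step 5. If the two assessments are individual.** Only 7 × 39 = €273 then depends on group size. At eight patients that part is 273/8 = €34.13. With 18 groups it is 273 × 18/150 = €32.76 (−€1.4). With 22 groups it is 273 × 22/150 = €40.04 (+€5.9). The occupancy effect shrinks accordingly.

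**The case against.** A reader might infer that 150 patients spread over the Madrid centres cannot fill groups of 8 to 10, and hence that €43.87 is wrong for the trial as run. The documents do not support either step. Nine evenly loaded centres fill their groups exactly, and an uneven spread over eleven can do so too. No section bars patients from different centres from sharing a group. The count of eleven is itself an inference: Amendment 5 does not say that its two Madrid centres joined this sub-study, and Amendment 4 places the sub-study in Valencia as well. The article is prospective and reports no realised group sizes.

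It is also fair to say that eight is the cautious end of 8–10, that about 8 and about 8–10 overlap, and that the amount at issue is a few euros on a component of about €44. No expected total cost or QALY difference is given against which to judge it. A price at planned size can also be defended as describing the programme as it would be delivered in routine care, and a sensitivity analysis is already planned.

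These arguments limit the size of the point but do not remove it. Fixed unit prices are used throughout the cost analysis, but elsewhere they multiply recorded quantities. Here the quantity is fixed as well. A planned-size price fits better as a named scenario than as the only value in the base case.

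**Conclusion.** The point holds in a limited form and is minor. The base-case price of TD-CBT is a planning constant, tied to one of two stated group sizes, with no link to delivery and no contribution to the bootstrap variance. The likely error in the arm mean is about -€2 to +€8 per patient if all €351 depends on group size, and about -€1.4 to +€5.9 (even spread) if the two assessments are individual. Both ranges rest on 9 to 11 centres, groups formed within a centre and at most 10 per group. Smaller groups through slow recruitment would push the cost higher, but the article gives no figures for that. The sign of the error cannot be fixed from the documents.

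**What to change.** In Description of Cost Analysis, replace the single €351/8 as follows:

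1. For each therapy group, compute (group sessions held × session price) / (number of patients allocated to that group) and assign the result to each of those patients. Using allocated rather than attending patients matches the intention-to-treat basis.
2. State whether the assessment sessions are individual. If they are, cost them separately and do not divide them by group size.
3. Use these patient-level values in the mean cost difference and in the bootstrap.
4. Keep €351/8 as a planned-size scenario in the sensitivity analysis.
5. Reconcile the group size of about 8 with 8–10.

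The cost is modest: a little more analysis work, and group membership and sessions held must be recorded, which the article does not say is done. The price may move slightly up or down through occupancy. Item 2 could matter more. If both assessments are individual, their cost per patient goes from 78/8 = €9.75 to 2 × 39 = €78, a rise of €68.25. That rise comes from how assessments are priced and is separate from group size, so it should be reported separately.
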